### 5.2. Stage 2 – Large-scale implementation and feasibility study

The primary analysis objective for Stage 2 is to estimate the proportion of patients with *P. vivax* malaria who correctly receive all components of revised case management (including G6PD testing, correct treatment with primaquine according to revised case management and G6PD activity, patient education, supervision of the first dose and community review at day 3), as stated in section 2.2.2. The secondary analysis objectives for Stage 2 include estimating the proportion of patients with secondary safety, tolerability and clinical review endpoints. The effectiveness and safety of implementing revised case management for patients with *P. vivax* malaria will also be estimated using an interrupted time series design for the incidence of symptomatic *P. vivax* malaria episodes, survival analysis of the cumulative risk of representation with *P. vivax* malaria and before versus

after analyses of the prevalence of asexual *P. vivax* parasitaemia and severe anaemia in patients presenting to health facilities with fever.

All of the above estimates will be presented with 95% confidence intervals.

## 6 Analysis sets/Subgroups

### 6.1. Stage 1 – Preliminary safety and feasibility study

The primary analyses of the endpoints in Stage 1 will include data from all patients enrolled across the four sites in PNG and Indonesia. Secondary analyses of patient-related study outcomes will be conducted overall and for the following prespecified subgroups:

- Patients from Indonesia, Papua New Guinea
- Study site
- Ethnic group
- Patients with G6PD activity >70%, ≥30% to ≤70% and <30%
- Patients prescribed PQ7, PQ14 and PQ8W
- Patients aged <5 years, 5-15 years and >15 years
- Males and females

### 6.2. Stage 2 – Large-scale implementation and feasibility study

The primary analysis of the endpoints in Stage 2 will include all patients enrolled across the 10 health facilities in Indonesia and Papua New Guinea from the start of the pre-implementation period to the end of the post-implementation period (estimated to be about 16,300 patients). Before versus after analyses of the prevalence of asexual *P. vivax* parasitaemia and severe anaemia from the cross-sectional surveys will be done on the full aggregated dataset of all patients enrolled in the surveys across the 10 study sites (aiming for 200 patients each health facility for each survey = 4,000 patients total).

Secondary analyses of patient-related study outcomes will be conducted for the following pre-specified subgroups:

- Patients from Indonesia & Papua New Guinea
- Patients from PNG, Indonesian Papua and Sumatra
- Study site
- Ethnic group
- Patients with G6PD activity >70%, ≥30% to ≤70% and <30%
- Patients prescribed PQ7, PQ14 and PQ8W
- Patients aged <5 years, 5-15 years and >15 years
- Males and females

All of the health facilities in the study are already collecting *P. vivax* malaria incidence data.

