**Secondary endpoints:**

*Quantitative measures of operational feasibility*

|        |                                                                                                                                                                                                                                                                                                                                                                                 |
|--------|---------------------------------------------------------------------------------------------------------------------------------------------------------------------------------------------------------------------------------------------------------------------------------------------------------------------------------------------------------------------------------|
| S2.SE1 | Proportion of health care practitioners who comply with the revised radical cure algorithm as defined below: 
 
Proportion of health care workers at the SCOPE health facility sites who correctly prescribe PQ (i.e. PQ7, PQ14 or PQ8W) according to the implementation package <math>\geq 95\%</math> of the time
 
              |
| S2.SE2 | Proportion of patients eligible for PQ who are tested for G6PD activity using the SD Biosensor at the time of their diagnosis of malaria.                                                                                                                                                                                                                                       |
| S2.SE3 | Proportion of eligible vivax malaria patients receiving the correct PQ regimen based on the result of the SD Biosensor test.                                                                                                                                                                                                                                                    |
| S2.SE4 | Proportion of vivax malaria patients who are ineligible for daily primaquine and are incorrectly prescribed an inappropriate primaquine regimen. 
Ineligible being defined as:
 
 
Infant <6 months or <5kg weight (Indonesia) or <1 year (PNG), pregnant women or women breastfeeding infants <6 months of age
 
 |

(Indonesia) or <1 year of age in PNG. Should not receive any primaquine

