- G6PD deficient (<30% enzyme activity). Should not receive daily primaquine.

S2.SE5 Proportion of vivax malaria patients that are reviewed on day 3.

S2.SE6 Proportion of vivax malaria patients that adhere to their prescribed primaquine regimen defined as follows:

- The proportion of patients who self-report that they have taken all prescribed PQ doses between the time of the initial prescription and the follow-up visit.

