### 3.2 Inclusion and exclusion criteria

**Inclusion criteria Stage 1 of the study (and thus receipt of either PQ7, PQ14 or PQ8w) are:** age >1 year (PNG) or ≥6 months (Indonesia), haemoglobin concentration ≥8 g/dl and signed agreement of patient or their carers to participate in the study and comply with all study-specific obligations, including attending follow-up clinical evaluations (at day 3 and day 7). Inclusion criteria for Stage 2 will be the same except that patients will only need to be able to attend a follow-up appointment (or receive a phone call) on day 3.

**Exclusion criteria:** pregnant and lactating females with infants <6 months in Indonesia and <1 year in PNG and patients with severe manifestations of malaria will not be prescribed primaquine and will not be enrolled in Stage 1. These patients will contribute incidence data to Stage 2 of the study but will not receive primaquine treatment. Patients' ineligible for primaquine treatment will be treated according to current national guidelines.

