#### 4.2.1 Revised and corrected Stage 2 power and precision calculations

Assumptions underlying the following Stage 2 power calculations include the following:

1. 5% of patients are ineligible for the intervention package (pregnancy, lactation, severe malaria, age <6m (Indonesia) or <1 yr (PNG)).
2. The impact on the risk and rate of infection will be the same across different endemic sites.
3. The mean baseline risk of *P. vivax* recurrence at 6 months is 20%
4. Loss to follow-up in both groups is 10%
5. Alpha = 0.05

During the 12-month pre-implementation period, a total of **17,160** patients with *P. vivax* (mono or mixed infections) presented to the ten study clinics (see Table 1). Assuming 5% of patients are ineligible for enrolment due to pregnancy, lactation or age under 6 months (Indonesia) or 12 months (PNG), this gives an estimated maximum number of patients eligible for recruitment into Stage 2 of **16,300**.

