| DOSING DEVIATIONS                                                                               |         |     |     |     |     |
| PQ7 n(%)                                                                                        |         |     |     |     |     |
| daily dose > 1.3mg/kg                                                                                  |         |     |     |     |     |
| daily dose < 0.5mg/kg                                                                                  |         |     |     |     |     |
| PQ14 n(%)                                                                                       |         |     |     |     |     |
| daily dose > 0.83mg/kg                                                                                 |         |     |     |     |     |
| daily dose < 0.25mg/kg                                                                                 |         |     |     |     |     |
| PQ8W n(%)                                                                                       |         |     |     |     |     |
| daily dose > 1.25mg/kg                                                                                 |         |     |     |     |     |
| daily dose < 0.38mg/kg                                                                                 |         |     |     |     |     |
|                                                                                                        |         |     |     |     |     |
| FOLLOW UP DEVIATIONS                                                                            |         |     |     |     |     |
| Proportion of Patients without Day3 Review (Day 3-5) N(% of all enrolled pts)                          |         |     |     |     |     |
| Proportion of Patients without Day7 Review (Day 6-10) N(% of all enrolled pts)                         |         |     |     |     |     |

Table S1a. Protocol deviations for patients enrolled in Stage 2 study by site

|                                                                                                        | Overall | HF1 | HF2 | HF3 | HF4 | HF5 | HF6 | HF7 | HF8 | HF9 | HF10 |
|--------------------------------------------------------------------------------------------------------|---------|-----|-----|-----|-----|-----|-----|-----|-----|-----|------|

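### The enrolled-patient analysis set does not fit the pregnancy, breastfeeding and infant part of S2.SE4

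*SAP*

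**What the plan says.** Section 2.2.2 defines S2.SE4 as: "Proportion of vivax malaria patients who are ineligible for daily primaquine and are incorrectly prescribed an inappropriate primaquine regimen". Two classes count as ineligible. The first is infants, pregnant women and women breastfeeding young infants, with the instruction "Should not receive any primaquine". The second is "G6PD deficient (<30% enzyme activity). Should not receive daily primaquine". No denominator is given beyond the words of the endpoint.

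Section 6.2 sets the population: "The primary analysis of the endpoints in Stage 2 will include all patients enrolled across the 10 health facilities" ("estimated to be about 16,300 patients"). Section 4.2.1 gives the source count, "a total of 17,160 patients with *P. vivax* (mono or mixed infections) presented to the ten study clinics" over 12 months, and removes 5% as ineligible for enrolment.

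Section 3.2 says of the excluded patients: "These patients will contribute incidence data to Stage 2 of the study but will not receive primaquine treatment". The Stage 2 deviation table in Appendix 3 (Table S1a) has the same scope as Section 6.2: "Protocol deviations for patients enrolled in Stage 2 study by site".

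**The concern.** The first class in S2.SE4 is made up of people whom the plan does not intend to enrol. A prescribing-error proportion needs every patient at risk of the error in the denominator, including those handled correctly. If the population is limited to enrolled patients, most of the at-risk group in this class is missing, and the missing patients are not a random sample of it. Those correctly refused primaquine are left out by design. Those wrongly prescribed it outside the study at the same clinics are also left out.

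S2.SE4 is the Stage 2 endpoint aimed at primaquine prescribed to patients who should not have it, and the study is meant to inform national policy. A result that looks reassuring for pregnant women and infants would carry little information if those women and infants were largely outside the data analysed.

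**Working it through.** **Inputs.** 17,160 vivax patients a year, 5% ineligible, 16,300 eligible and 11,410 anticipated at 70% recruitment (Sections 4.2 and 4.2.1); 16,302 (Table 1 total); 16,300 as the analysis set (Section 6.2); 764 of 800 with G6PD >70% (Section 4.1).

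**Reproducing the plan's figure.** The ten clinics in Table 1 sum to 17,160. 17,160 × (1 − 0.05) = 16,302, which rounds to the stated 16,300. 0.70 × 16,300 = 11,410 also reproduces. Both sizes are therefore counts of eligible patients only.

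**Who was removed.** 17,160 × 0.05 = 858. The text under the assumptions in Section 4.2.1 and the Table 1 footnote attribute the 5% to pregnancy, lactation and young age. Assumption 1 in the same section adds severe malaria, which is not an S2.SE4 category, so 858 is an upper figure for the first class.

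**What the enrolled set then yields for this class.** If enrolment follows the criteria, the result is 0 of 0 at any prescribing rate. If some are enrolled in error, the proportion depends on why they were enrolled, which the SAP does not describe.

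**What a full denominator would yield.** The true rates below are assumptions. Wrong prescriptions = 858 × rate; 95% half-width = 1.96 × √(p(1 − p)/858). The last column divides the same events by 16,302, as if every wrongly treated patient had been enrolled.

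| Assumed rate | Events | Share of the 858 (95% half-width) | Share of 16,302 |
|---|---|---|---|
| 1% | 8.6 | 1% (0.7 points) | 0.05% |
| 5% | 42.9 | 5% (1.5 points) | 0.26% |
| 20% | 171.6 | 20% (2.7 points) | 1.05% |

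**The G6PD <30% class.** These patients are not listed in the 5%. Section 3.1.1 assigns them the 8-week regimen, Section 3.1.2 carries the procedures into Stage 2, Section 6.2 names them as a subgroup, and Table S1a has rows for PQ7 or PQ14 given to them. The SAP states no prevalence. An assumed range of 0.5% to 4.5% uses as its upper end the plan's own share at or below 70% activity: (800 − 764)/800 = 4.5%. Among 11,410 this gives about 57 to 513 patients. The 95% half-width, 1.96 × √(p(1 − p)/n), is 3.6 to 1.2 points at a 2% error rate and 10.4 to 3.5 points at 20%. The normal approximation is rough at the small end, but 2% and 20% can be told apart. This part of the endpoint is estimable as planned.

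**The case against.** The strongest reply is that Section 6.2 should not be read so strictly. It speaks of patients enrolled from the start of the pre-implementation period, before the package existed, so the word is used loosely. S2.SE4 itself speaks of vivax malaria patients, and Section 9.2 presents related outcomes for all patients. Several endpoints name populations that differ from Section 6.2. Section 3.2 does not say that the excluded patients contribute incidence data and nothing else, and its explicit statement about non-enrolment refers to Stage 1.

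These points show that a wider denominator is possible, not that the plan fixes one. Section 4.2.1 calls these patients ineligible for enrolment. The phrase in Section 9.2 is undefined and follows a reference to eligible patients. Where another population is meant, as for S2.SE17 and S2.SE18, the SAP describes it. For S2.SE4 it does not.

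Other parts of the reply do stand, and they rule out stronger readings that a reader might infer:

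- That S2.SE4 as a whole cannot separate good prescribing from bad. The G6PD <30% class is enrolled and can be assessed.
- That the first class must show close to 100% error. This needs such patients to be enrolled only when primaquine is prescribed. The SAP does not say so, and Table S1a lists each class with treated patients as a sub-row, which leaves room for untreated ones.
- That dividing by all enrolled patients hides any difference. 0.05% and 1.05% of about 16,300 have 95% half-widths of about 0.03 and 0.16 points and are clearly distinguishable. The share of ineligible patients wrongly treated is still not what is reported, and unenrolled patients remain uncounted.
- That the two classes are pooled. The SAP never says this, and Table S1a gives them separate rows.
- That Table S1a reports S2.SE4. It is a deviation table and is not tied to the endpoint.

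**Conclusion.** The point holds for one of the two classes in S2.SE4. Followed as written, Section 6.2 analyses a set from which pregnant women, breastfeeding women and infants have been removed by the plan's own arithmetic. Their prescribing-error proportion therefore lacks its denominator and misses errors among unenrolled patients. The group left out is up to about 858 a year. That figure rests on the plan's 5% assumption, includes an unknown number with severe malaria, and comes from a count that Table 1 labels as episodes.

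The wrongful-prescribing rates used above are illustrative, as the SAP gives none. The G6PD <30% class is unaffected. The primary endpoint and the other secondary endpoints are not in question here, and no treatment rule is judged.

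**What to change.** In Section 6.2 and in the definition of S2.SE4, give the endpoint its own analysis set and report two separate proportions.

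- **(a) Pregnant women, breastfeeding women and infants as S2.SE4 defines them.** Denominator: all vivax patients recorded as such in facility records at the ten sites after the start of Stage 2, enrolled or not. Numerator: those prescribed any primaquine. Show the number with unknown pregnancy or lactation status.
- **(b) Patients with a recorded G6PD result <30%.** Denominator: all such tested patients. Numerator: those prescribed daily primaquine.

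Part (b) should stay with tested patients because the SAP does not show that surveillance holds G6PD results for unenrolled patients.

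The cost is SAP wording and one tabulation. For (a), Section 3.1 says the facility records hold demographics, diagnosis and treatment. Section 11 already plans to screen unenrolled patients on age, pregnancy and lactation and to tabulate reasons for non-eligibility. The downside is that pregnancy and lactation may be recorded less completely for unenrolled patients, which is why the unknowns need to be shown.

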## 7 Outcomes and Covariates

The primary, secondary and exploratory outcomes for Stage 1 and Stage 2 are defined in Section 2.2 (Endpoints).

Intervention and covariate variables for analyses of the impact of the implementation package on incidence of symptomatic *P. vivax* malaria (effectiveness outcome S2.SE15) will be defined as follows:

- a) **Level change** intervention effect (i.e. change in mean monthly incidence) 6 months after the start of stage 2; Figure 2, Section 9.
- b) **Slope change** intervention effect (i.e. change in the rate of change of monthly incidence) immediately after the start of stage 2; Figure 2, Section 9.

Intervention will take the value of 1 for all time points following the start of stage 2 implementation at each health facility site, and a value of 0 for all other timepoints for both the level and slope changes.

The time month covariate will be defined as the number of months after the start of stage 2 implementation (Appendix 4: Figure 1), i.e. negative values for pre-implementation and positive values for post-implementation.

Seasonality will be captured using spline terms for the Indonesian health facility sites and the PNG health facility sites.

Any unexpected stock outages or major, discrete malaria control interventions external to the SCOPE project will also be captured and reported by health facility site and calendar time month.

The key covariates that will be included in the analyses of the safety and exploratory outcomes will be the haemoglobin concentration at enrolment, the mg/kg dose of primaquine and the G6PD enzyme activity. Key covariates to be adjusted for in the analysis of patient-level effectiveness outcomes will be baseline age, weight and sex, except in the case that these variables have already been considered in a propensity score matching process.

## 8 Handling of Missing Values

We do not expect there to be any reason that calendar time month will be missing for any observations over the study period (pre-implementation, Stage 1 and Stage 2) at each of the 10 sites. This is based on our experience of routine data collection during the baseline data period (i.e. prior to pre-implementation stage). We will descriptively report the patterns of missingness for the outcome measures and other participant variables over time in each site. For all analyses, missing data will be handled using an available case analysis, i.e. missing data on any variable included in the analysis where the observation for an individual at that time point is missing is excluded from the analysis.

## 9 Statistical Methodology

Continuous surveillance and pharmacovigilance data will be summarised and presented to study staff in graphical and descriptive text format on a monthly basis to enable real-time feedback on case numbers and distributions, data integrity, clinical performance and revised case management adherence.

### 9.1. Stage 1 – Preliminary safety and feasibility study

For Stage 1, the number and proportion of patients experiencing at least one SAE (S1.PE1) or at least one AESI (S1.PE2) will be computed by treatment arm (PQ7, PQ14, PQ8w), and described in summary tables which will include breakdown by type of event, severity, relatedness to treatment, and timing of occurrence (see Appendix 4 for example Tables 1-4). The number and proportion of patients permanently discontinuing treatment (S1.SE4) will be computed by treatment arm and presented in a summary table, with breakdown of reason for discontinuation. Absolute numbers of AESIs with denominators (S1.PE1-3) and proportions with 95% confidence intervals (calculated using a binomial distribution) will be presented in tabular and graphical format. A full tabulation of all SAEs will also be presented.

For S1.EE3, the number and proportion (and 95% Confidence Interval) of patients observed to have a >25% reduction in haemoglobin to a concentration below 7 g/dl will be computed by treatment arm (PQ7, PQ14, PQ8w), and described in summary tables.

For S1.EE1 and S1.EE2, the unadjusted and adjusted mean absolute and proportional maximum change in haemoglobin within 7 days (95% CI) respectively will be presented by treatment arm (PQ7, PQ14, PQ8w). The adjusted means will be estimated from a linear regression model that adjusts for baseline haemoglobin level and G6PD enzyme activity level. The association between change in haemoglobin from baseline to day 2 and G6PD enzyme activity level will be estimated from a linear regression model that allows for a nonlinear association using fractional polynomials and adjusts for baseline haemoglobin level, age, sex and baseline parasitaemia. A scatterplot of the data will be presented with observations labelled by treatment arm (PQ7, PQ14, PQ8w).

For S1.EE4, the mean difference, standard deviation of the difference and 95% limits of agreement between Biosensor and HemoCue haemoglobin measurements will be computed using Bland-Altman plots (Bland JM & Altman DG 1995), stratified by day of measurement (day 0, 3, 7) and country. The data will be presented in tabular and graphical formats.

For S1.EE5, the distribution of methaemoglobin at baseline, day 3 and day 7 will be presented by treatment arm (PQ7, PQ14, PQ8w) using box and whisker plots. The distribution of methaemoglobin levels at day 7 will be compared between the PQ7 (daily PQ dose of 1mg/kg) and PQ14 (daily PQ dose of 0.5 mg/kg) treatment arms using linear regression after adjusting for baseline haemoglobin concentration, parasitaemia, age, sex, and G6PD enzyme activity level.

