#### 2.1.1. Stage 1 – Preliminary safety and feasibility study

**Primary objective:**

- S1.PO1 To determine the safety of PQ in patients prescribed different treatment regimens
- S1.PO2 Determine the risk of patients experiencing any AESI during treatment

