#### **Primary endpoints:**

- |        |                                                                                                              |
|--------|--------------------------------------------------------------------------------------------------------------|
| S1.PE1 | Proportion of patients experiencing at least one SAE during treatment.                                       |
| S1.PE2 | Proportion of patients experiencing at least one AESI, SAE or other AE of at least grade 3 during treatment. |

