**Table 5. Number of patients with at least one event enrolled in Stage 1 safety and feasibility study by treatment arm**

|                                   | Overall | PQ7 | PQ14 | PQ8W |
|-----------------------------------|---------|-----|------|------|
| Total Enrolled N           |         |     |      |      |
| Flagged Day 3-5 N(%) *            |         |     |      |      |
| Flagged Day 6-10 N(%) *           |         |     |      |      |
| Other Day Flagged N(%) *          |         |     |      |      |
|                                   |         |     |      |      |
| Aes n(%)                   |         |     |      |      |
| Total Grade 3                     |         |     |      |      |
| Total Grade 4                     |         |     |      |      |
| Total                      |         |     |      |      |
| AESI                       |         |     |      |      |
| Haemolysis                 |         |     |      |      |
| AESI (SAE)                        |         |     |      |      |
| AESI (NonSAE)                     |         |     |      |      |
| Total                      |         |     |      |      |
| Gastrointestinal           |         |     |      |      |
| AESI (SAE)                        |         |     |      |      |
| AESI (NonSAE)                     |         |     |      |      |
| Total                      |         |     |      |      |
| Methaemoglobinaemia        |         |     |      |      |
| AESI (SAE)                        |         |     |      |      |
| AESI (NonSAE)                     |         |     |      |      |
| Total                      |         |     |      |      |
| SAEs                       |         |     |      |      |
| SAE – definitely related          |         |     |      |      |
| SAE – probably related            |         |     |      |      |
| SAE – possibly related            |         |     |      |      |
| SAE – unlikely related            |         |     |      |      |
| SAE – not related                 |         |     |      |      |
| Total                      |         |     |      |      |
| Related SAE which is also an AESI |         |     |      |      |
| Related SAE Other                 |         |     |      |      |

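### Stage 1 primary endpoint S1.PE2 is a composite in Section 2.2.1 but AESI only in Section 9.1 and in objective S1.PO2; the three must be reconciled.

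*SAP*

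**What the plan says.** Section 2.1.1 gives the matching primary objective as "S1.PO2 Determine the risk of patients experiencing any AESI during treatment".

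Section 2.2.1 lists two primary endpoints. S1.PE1 is "Proportion of patients experiencing at least one SAE during treatment". S1.PE2 is "Proportion of patients experiencing at least one AESI, SAE or other AE of at least grade 3 during treatment".

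Section 7 states that the Stage 1 and Stage 2 outcomes are those defined in Section 2.2.

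Section 9.1 then plans the analysis: the number and proportion of patients with an SAE, for S1.PE1, or with "at least one AESI (S1.PE2) will be computed by treatment arm (PQ7, PQ14, PQ8w"). Its sentence on intervals reads "Absolute numbers of AESIs with denominators (S1.PE1-3) and proportions with 95% confidence intervals (calculated using a binomial distribution"). No S1.PE3 is defined. The section sends the reader to Appendix 4 for example Tables 1-4, but the dummy tables are in Appendix 3.

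The by-arm shell is "Table 5. Number of patients with at least one event enrolled in Stage 1 safety and feasibility study by treatment arm". Like Table 4, which is by health facility, it has separate blocks for AEs of grade 3 and 4, for AESIs by type, and for SAEs by relatedness.

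**The concern.** One label on a primary safety endpoint covers two different events. A programmer working from Section 9.1 would count AESI patients only. One working from Sections 2.2.1 and 7 would count patients with an AESI, an SAE or another AE of grade 3 or above. The two counts can differ, and so can their confidence intervals.

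The narrower version leaves two groups out of S1.PE2. Patients whose only event is a non-AESI SAE remain visible in S1.PE1. Patients whose only event is a non-serious, non-AESI AE of grade 3 or above belong to no other Stage 1 event-rate endpoint with a planned interval.

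While both definitions stand, the version to be reported is not fixed, and the SAP does not show which one has been used.

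**Working it through.** **1. The definitions side by side.**

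| Place in the SAP | Event counted |
|---|---|
| Section 2.1.1, objective S1.PO2 | AESI |
| Section 2.2.1, endpoint S1.PE2 | AESI, or SAE, or other AE of grade 3 or above |
| Section 7 | as in Section 2.2 |
| Section 9.1, analysis labelled S1.PE2 | AESI |

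The longer wording in Section 2.2.1 does not look like a slip for AESI only. Where the plan wants an AESI-only endpoint it writes one, as in S2.SE10 for Stage 2.

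**2. Direction of the difference.** Let A be the patients with an AESI, S those with an SAE, G those with another AE of grade 3 or above, and N the denominator.

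- Section 9.1: p(9.1) = |A| / N
- Section 2.2.1: p(2.2.1) = |A ∪ S ∪ G| / N
- Gap: p(2.2.1) − p(9.1) = (number of patients in S or G but not in A) / N ≥ 0

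The gap is zero only if every patient with an SAE or another AE of grade 3 or above also has an AESI. The plan foresees that this may not be so: its event tables separate related SAEs that are also AESIs from other related SAEs, and have rows for SAEs judged unlikely to be related or not related. S1.PE2 has no relatedness restriction.

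**3. Whether the dummy tables repair it.** They do not.

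- Tables 4 and 5 have no row for the union of the three event classes. They also have no row for any AESI across the three AESI types.
- The blocks overlap: each AESI type has a line for AESIs that are also SAEs, and those patients recur in the SAE block. Adding the blocks counts patients more than once, so the sum is only an upper bound.
- Table 5 is the only event table by treatment arm, and it lies outside the range of tables cited in Section 9.1.

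**4. Size.** The SAP states no figure for S1.PE2 to reproduce. The only Stage 1 precision figure, ±1.55% in Section 4.1, concerns stopping therapy: 1.96 × √(0.05 × 0.95 / 764) = 1.545%. It reproduces, but does not bear on this endpoint.

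As an illustration only, take N = 800 (Section 4.1) and **assume** 16 AESI patients, giving 16/800 = 2.0%. Let e be the assumed number of further patients with only a non-AESI SAE or another AE of grade 3 or above. The intervals are exact binomial: with x = 16 + e, the lower limit is the 0.025 quantile of Beta(x, N − x + 1) and the upper limit is the 0.975 quantile of Beta(x + 1, N − x).

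| e (assumed) | AESI only (Section 9.1) | Composite (Section 2.2.1) | Gap e/800, percentage points |
|---|---|---|---|
| 0 | 2.0% (1.1 to 3.2) | 2.0% (1.1 to 3.2) | 0 |
| 8 | 2.0% (1.1 to 3.2) | 3.0% (1.9 to 4.4) | 1 |
| 16 | 2.0% (1.1 to 3.2) | 4.0% (2.8 to 5.6) | 2 |
| 24 | 2.0% (1.1 to 3.2) | 5.0% (3.6 to 6.7) | 3 |

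These counts are chosen to show how the gap behaves. They are not predictions.

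**The case against.** The best defence is that Section 9.1 is shorthand. Section 7 makes Section 2.2 the source of definitions, Section 9.1 cites the label S1.PE2, and the section is loose elsewhere (the reference to S1.PE1-3 and the wrong appendix). The table shells are described as examples, so a missing row does not rule out an output. A careful analyst could therefore arrive at the composite. This makes a wrong result avoidable, but it does not remove the contradiction. Section 9.1 spells out the event it will count, its interval sentence again names only AESIs, and S1.PO2 agrees with it.

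A reader might infer three stronger things that the SAP does not support.

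- *That events are hidden.* They are not. SAEs have their own primary endpoint and a full tabulation, and AEs of grade 3 and 4 have rows in Tables 3 to 5. What is affected is one summary proportion and its interval.
- *That the move to Stage 2 rested on a figure that was too low.* Section 3.1.1 leaves the progression criteria to the Safety Monitoring Committee. They are not in this document, and nothing ties them to S1.PE2. Section 11 describes the start of Stage 2 in the past tense, so a correction to version 9.0 (11-NOV-2025) appears to bear on reporting and not on that decision.
- *That the shortfall is known to be large.* No event rate is given from which to say so.

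It is also fair to say that the composite need not be what was intended, since the objective and the analysis section both point to AESI only.

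**Conclusion.** The inconsistency is real. Two incompatible events carry the label of one Stage 1 primary endpoint, and no part of the SAP reconciles them. Under Section 7 the composite governs. Measured against it, Section 9.1 as written gives a proportion that is equal or lower in every possible dataset. That conclusion rests on set logic alone.

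The size of the gap is unknown and may be zero. The range of 0 to 3 percentage points above depends wholly on assumed counts.

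This should be fixed before final Stage 1 reporting. It is not grounds for doubting the safety review already done: Stage 1 is descriptive, no sample size or test depends on S1.PE2, and the component events remain on display.

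**What to change.** - **Section 9.1:** compute S1.PE2 as defined in Section 2.2.1, by treatment arm and overall, with 95% confidence intervals. Show the AESI-only proportion as a labelled component.
- **Tables 4 and 5:** add two rows that count each patient once, one for any AESI and one for any AESI, SAE or AE of grade 3 or above.
- **Section 2.1.1:** align S1.PO2 with the endpoint.
- **Section 9.1 references:** correct S1.PE1-3, and point to Appendix 3 and to a table range that includes Table 5.
- **If AESI only was intended:** restate S1.PE2 in Section 2.2.1 with a dated reason in the revision history, and report the composite as well. Stage 1 appears to be complete, so showing both removes any doubt about choosing a definition after the results.

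The cost is a few lines of SAP text and two table rows. The plan already tabulates every component, so no new data are needed.
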